## Abstract

**Background:**

New approaches on paediatric cancer treatment aim to maintain long-term health. As a result of radiotherapy, chemotherapy or surgery, paediatric cancer survivors tend to suffer from any chronic health condition. Endocrine dysfunction represents one of the most common issues and affects bone health. Exercise is key for bone mass accrual during growth, specifically plyometric jump training. The iBoneFIT study will investigate the effect of a 9-month online exercise programme on bone health in paediatric cancer survivors. This study will also examine the effect of the intervention on body composition, physical fitness, physical activity, calcium intake, vitamin D, blood samples quality of life and mental health.

**Methods:**

A minimum of 116 participants aged 6 to 18 years will be randomized into an intervention (*n* = 58) or control group (*n* = 58). The intervention group will receive an online exercise programme and diet counselling on calcium and vitamin D. In addition, five behaviour change techniques and a gamification design will be implemented in order to increase the interest of this non-game programme. The control group will only receive diet counselling. Participants will be assessed on 3 occasions: 1) at baseline; 2) after the 9 months of the intervention; 3) 4 months following the intervention. The primary outcome will be determined by dual energy X-ray absorptiometry (DXA) and the hip structural analysis, trabecular bone score and 3D-DXA softwares. Secondary outcomes will include anthropometry, body composition, physical fitness, physical activity, calcium and vitamin D intake, blood samples, quality of life and mental health.

**Discussion:**

Whether a simple, feasible and short in duration exercise programme can improve bone health has not been examined in paediatric cancer survivors. This article describes the design, rationale and methods of a study intended to test the effect of a rigorous online exercise programme on bone health in paediatric cancer survivors. If successful, the iBoneFIT study will contribute to decrease chronic health conditions in this population and will have a positive impact in the society.

**Trial registration:**

Prospectively registered in isrctn.com: isrctn61195625. Registered 2 April 2020.

## Background

Owing to major advances in cancer screening and treatment over the last 30 years, cancer survival has improved dramatically. In Europe, the paediatric cancer incidence increases annually by 0.54% in children (0–14 years) and by 0.96% in adolescents (15–19 years), although it seems that the incidence in adolescents is decelerating [1]. Nevertheless, the 5-year survival rate is now at 77.9% for children and 79% for adolescents and young adults (20–39 years) [2, 3]. Unfortunately, the treatment of paediatric cancer by means of radiation, chemotherapy and/or surgery is associated with various late effects (e.g. impaired growth, musculoskeletal sequelae, cardiopulmonary compromise and secondary malignancy) [4–6], predisposing paediatric cancer survivors to disabling conditions [4]. Furthermore, paediatric cancer treatment has been documented to have an effect on emotional well-being and quality of life, with survivors reporting anxiety, depression and post-traumatic stress [7, 8].

Paediatric cancer is a life-threatening condition that also occurs during the period of bone development and strengthening. Gonadal failure following to pelvic radiation or gonadotoxic chemotherapy and hypothalamic pituitary dysfunction by means of cranial radiation can adversely affect areal bone mineral density (aBMD), increasing osteoporosis risk later in life [9, 10]. In addition, direct radiation to bone not only causes hypovascularity but has a direct cytotoxic effect on the epiphyseal chondrocytes [11]. Observational studies have found low aBMD during and after cancer treatment to be associated with increased fracture risk (80% increase for every 1 SD reduction in lumbar spine aBMD Z-score) [12–15], which can lead to a higher risk of osteopenia and osteoporosis in adulthood and finally, disability [16, 17]. Moreover, data from a review showed that up to 68% of paediatric cancer survivors presented moderate-to-severe aBMD deficits (Z-score < − 1), while up to 46% had severe aBMD deficits (Z-score < − 2) [18].

The attainment of peak bone mass during childhood and adolescence determines the aBMD later in life and therefore the onset of osteoporosis [19, 20]. This process has a strong genetic component, although lifestyle factors (i.e. physical activity and dietary habits) contribute up to 20% of the variation in peak bone mass [21]. High-intensity, weight bearing physical activity that elicit a variety of strains and include multiple rest periods is known to improve bone mass [22–25], accrual [26] and maintenance [27] as the skeleton adapts to the loads under which it is placed. Likewise, an adequate calcium and vitamin D intake in combination with physical activity is necessary to obtain beneficial gains in bone health in children and adolescents [28, 29]. In this sense, calcium and vitamin D supplementation did not add benefit to nutritional counselling for improving bone outcomes among adolescents and young adults survivors of acute lymphoblastic leukaemia [30].

### Exercise and bone health

Exercise contributes to the development of bone mass in youths due to its association with increases in lean mass [31, 32]. Larger muscles exert greater forces on the bones, which will adapt and therefore improve their strength [33]. Furthermore, plyometric jump training is one of the best methods to improve bone health since the impacts produced against the ground will cause higher forces on the bones [34]. A recent systematic review has shown that plyometric jump training causes improvements in bone mineral content (BMC), aBMD and structural properties in children and adolescents [35]. More specifically, an 8-month jumping intervention (~ 3 min/day) improved bone mass in the proximal femur in pubertal children [36]. Mackelvie et al. [37] showed that a 7-month jumping intervention (10 min, 3 times/week) enhanced bone mass in the femoral neck and lumbar spine in pubertal girls. Additionally, Vlachopoulos et al. [38, 39] found that a 9-month jumping intervention (10 min, 3 to 4 times/week) improved bone outcomes in adolescent males participating in non-osteogenic sports and with poorer bone health.

A similar effect might be seen in survivors of paediatric cancer. A randomized controlled trial (RCT) in children with acute lymphoblastic leukaemia showed that resistance exercise was unsuccessful in preventing the reduction in aBMD [40]. However, the intervention (duration, load) was not properly described. A RCT focusing on low-magnitude, high frequency mechanical stimulation seemed to improve total body aBMD in paediatric cancer survivors, while a reduction was observed in the placebo group [41]. In a recent study in children with cancer, the exercise programme was not successful in improving aBMD nor other factors such as physical function or health-related quality of life [42]. This was because exercise requires of certain intensity to modify these factors and this could not be achieved during treatment due to the child’s responses to the treatment and disease. Considering the gap in the literature, and taking into account the Exercise Guidelines for Cancer Survivors [43, 44], it is crucial to develop and implement feasible exercise programmes focused on improving bone health into survivorship.

The aim of this study is to investigate the effect of a 9-month online exercise programme on bone health in paediatric cancer survivors aged 6–18 years and to follow up these outcomes 4 months after the intervention to determine the extent of residual effect. We hypothesize that the intervention stimulus will be enough to improve bone health in this population. We will also examine the effect of the intervention on body composition, physical fitness, physical activity, calcium intake, vitamin D, blood samples quality of life and mental health.

## Methods/ design

### Study design

This protocol is reported based on Standard Protocol Items: Recommendations for Interventional Trials (SPIRIT) guidelines [45]. The iBoneFIT study is a multi-centre, parallel groups RCT (1:1) designed under the equivalence basis and registered in isrctn.com (Reference: isrctn61195625, 2 April 2020). Eligible participants from two paediatric oncology units of Southern Spain will be contacted, informed, and if consenting, enrolled into the study after a meeting (T_− 1_) (see recruitment section). Then, randomization will be performed by an external partner who is independent of the participant recruitment and enrolment process (see randomization section). Assessments will be conducted at baseline (T_0_) and after nine (T_1_) and thirteen (T_2_) months in the Sport and Health University Research Institute (iMUDS, University of Granada). After finishing the study, participants in the control group will be offered the same online exercise programme. A graphical description of the study design is shown in Fig. 1.

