### Recruitment

Eligible participants will be contacted via telephone calls or information letters from the Units of Paediatric Oncology of the ‘Virgen de las Nieves’ (Granada) and ‘Reina Sofía’ (Córdoba) University Hospitals in Southern Spain. A short study information brochure will be used in routine check-ups. A meeting will be held with potential participants and parents/tutors to carefully inform about the benefits and risks of the study, and researchers will answer any question that they may have. Then, informed consents will be given, and participants will have 15 days to send it to the researchers. A hotline will be available to clarify remaining questions about the study. Those who do not react to the study invitation will be followed up via phone call at the end of these 15 days in order to check if they wish to participate. All participants will sign the informed consent before their visit to the iMUDS.

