### Randomization and blinding

Randomization to an intervention group (online exercise programme, IG) or control group (no treatment, CG) will be performed by an external partner ([name]) who is independent of the participant recruitment and enrolment process, stratified by age and sex. Each participant will be provided a uniform (0, 1) random number using SAS software, version 9.1 (SAS Institute Inc), within their respective age and sex group. Assignments will be blinded to the assessors until all tests are completed. For feasibility reasons, the study will probably be conducted in two waves of 58 children at most.

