### Statistical analysis

All variables will be checked for normality using both statistical and graphical methods. Results will be presented as frequencies and proportions with 95% confidence intervals for categorical variables and mean (standard deviation) or median (range) for continuous variables. A descriptive analysis of the participants characteristics will be performed as soon as the baseline assessments are completed. This cross-sectional analysis will show the comparability of IG and CG and the need for adjustment when between group comparisons are done.

General Lineal Models will be used to examine the training effects [time (pre-post 9-month intervention) x group interaction] on the primary and secondary outcomes. Change in bone outcomes will be used as age and sex-adjusted z-scores. The baseline level of each outcome variable will be entered as covariate. Effect sizes will be reported. Multiple imputation methods and sensitivity analysis (i.e. propensity score) will be performed to handle missing data and appreciate the potential influence of missing responses. Finally, in the event of possible dropouts, a statistical analysis will be carried out by protocol and intention to treat.

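### The protocol article places randomisation before the baseline assessment and does not say that families stay unaware of the arm until baseline is complete

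*Protocol article*

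**What the plan says.** The Study design section describes the steps in sequence. Eligible families are "contacted, informed, and if consenting, enrolled into the study after a meeting" (T-1). The next sentence begins "Then, randomization will be performed by an external partner who is independent of the participant recruitment and enrolment process". The one after it begins "Assessments will be conducted at baseline" (T0) and goes on to the nine- and thirteen-month visits and their location. The Recruitment section adds that "All participants will sign the informed consent before their visit to the iMUDS", the site where the assessments take place.

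On masking, the Randomization and blinding section says "Assignments will be blinded to the assessors until all tests are completed". It does not mention children or parents. Strata are age and sex only.

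The Statistical analysis section gives baseline a central role: "The baseline level of each outcome variable will be entered as covariate". It also plans a comparison of the arms at baseline: "This cross-sectional analysis will show the comparability of IG and CG and the need for adjustment when between group comparisons are done". For incomplete data it states "Multiple imputation methods and sensitivity analysis (i.e. propensity score) will be performed to handle missing data", and it plans both per-protocol and intention-to-treat analyses if there are dropouts.

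**The concern.** Adjusting for a baseline value is safe when allocation cannot have influenced that value. Measuring baseline before the arm is known guarantees this. The written order does not.

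An online jumping programme compared with diet advice alone cannot be masked once a family has been told the arm. If that happens before T0, it can alter effort in the shuttle runs, long jump and handgrip, behaviour during the accelerometer week, and answers on calcium intake, quality of life, anxiety, depression and affect. The altered baseline then enters the model as a covariate.

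The second issue is loss. A child who learns the arm and withdraws before T0 has been randomised but never measured. If disappointment at being a control is the reason, the loss differs by arm. That child has no DXA scan either, so this route reaches the primary outcome.

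**Working it through.** **1. Order of steps.** No stated figure decides this point, so the sections are set side by side.

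| Step | Section | What it establishes |
|---|---|---|
| Meeting, consent, enrolment | Study design; Recruitment | Consent precedes the visit to the assessment site, so enrolment can be complete before any measurement |
| Randomisation | Study design | Follows enrolment, marked by a sequence word |
| T0 | Study design | Listed after randomisation, with no sequence word or date of its own |
| Blinding | Randomization and blinding | Assessors only; fits either order |
| Comparison of arms at baseline | Statistical analysis | Fits either order |

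No section places randomisation after T0, and none says when families are told the arm. The strata, age and sex, are known at enrolment. Nothing measured at T0 is therefore needed in order to randomise, and nothing in the scheme prevents randomisation from waiting for T0.

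**2. Which outcomes are exposed.** The primary outcome comes from DXA scans, which depend on neither effort nor self-report. The exposed outcomes are the fitness battery and perceived-fitness scale, accelerometry and activity recall, the calcium and vitamin D questionnaires, and the quality-of-life and mental health scales.

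**3. Effect of a shifted baseline.** Suppose knowledge of the arm raises the measured baseline in the exercise arm, relative to control, by s (in SD units), and the shift does not carry over to the later measurement. With baseline as covariate and slope b of the later value on baseline:

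bias in the adjusted effect ≈ −b × s

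Modelling change instead of the later value gives the same result once baseline is a covariate. Change without the covariate would be biased by −s. For b between 0 and 1, the adjusted bias therefore lies between 0 and s in size.

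The only correlation in the article is 0.7, assumed in the Sample size section for femoral neck aBMD. The documents give none for the exposed outcomes. Purely as an illustration, with b = 0.7 (which also requires equal SDs at both times) and assumed shifts:

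- s = 0.05: 0.7 × 0.05 = 0.035 SD
- s = 0.10: 0.7 × 0.10 = 0.07 SD
- s = 0.20: 0.7 × 0.20 = 0.14 SD

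These figures show how the formula behaves and do not estimate the bias in this trial. For DXA measures, s near 0 is plausible.

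**4. Loss before T0.** The planned size is 58 per arm. If 5% of controls left on learning their arm (an assumption; the documents give no rate), 0.05 × 58 = 2.9, or about 3 children, would have no data. For such a child, imputation could draw on little beyond age, sex and arm.

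**The case against.** The strongest reply is that generating an allocation and disclosing it are separate acts, and the article is silent on the second. A reader might infer that children know their arm when baseline is measured. The documents do not say so. The T0 sentence lists all visits and their location without an explicit link to randomisation, and Fig. 1, which the article cites for the design, is not available here and might settle the order either way. This objection stands: families may know the arm, and nothing more can be claimed.

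A reader might also infer that children without a baseline are excluded from the intention-to-treat analysis. That does not hold, because multiple imputation is planned. An assumed loss of about 3 of 58 is also well within the 20% allowance for losses and refusals in the Sample size section, so power is not the issue. What remains is that imputing a child with no measurements adds almost nothing, and that loss triggered by allocation would be differential.

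Finally, effort-based and self-reported outcomes in an open exercise trial are unmasked at nine and thirteen months whatever the order. That is true, and reordering does not cure it. It does protect the baseline, which is the part the design can protect at almost no cost.

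**Conclusion.** The point holds in limited form. The only written order puts randomisation after enrolment and before T0, and the article does not say that allocation is withheld from families until T0 is complete. The baselines of effort-dependent and self-reported secondary outcomes are therefore open to influence by allocation, and children could be lost, differentially by arm, before any measurement.

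It would go too far to conclude that the primary bone result is biased through its baseline: assessors are blinded and scans hardly respond to expectation. The primary outcome is touched only through loss before T0.

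The size cannot be derived from the documents. It depends on when families are told, on the shift s and slope b for each exposed outcome, and on any withdrawal rate between allocation and T0, none of which is given. This is a cheap improvement to the design and does not invalidate it.

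**What to change.** State and follow the order T-1, then T0 including the accelerometer week and all questionnaires, then randomisation. If allocations must be generated earlier for practical reasons, the external partner should at minimum release them to families only once that child's T0 is complete. The text should say so, and should also say how any child randomised without a baseline is handled in the intention-to-treat analysis.

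The cost is one reordered step. The allocation is released about a week later, which is the length of the seven-day accelerometer wear. Stratification, sample size and the analysis model need no change.

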**Fig. 1 Fig1:**
[figure not shown]
iBoneFIT study design. T_− 1_, meeting with parents and participants; T_0_, baseline assessment; T_1_, post-intervention assessment; T_2_, follow-up assessment. iMUDS *Sport and Health University Research Institute*

### Ethical approval

The study will be performed following the ethical guidelines of the Declaration of Helsinki, last modified in 2013. This study has been checked and approved by the Ethics Committee on Human Research of Regional Government of Andalusia (Reference: 4500, December 2019).

### Inclusion and exclusion criteria

The iBoneFIT study will include paediatric cancer survivors: 1) aged 6 to 18 years; 2) diagnosed at least 1 year earlier; 3) to have been exposed to radiotherapy and/or chemotherapy; and 4) not currently receiving treatment for cancer.

Exclusion criteria are defined as follows: 1) simultaneous participation in another study that place participants at any additional risk, discomfort or affect the results of both studies; 2) previous diagnosed anorexia nervosa/bulimia, known pregnancy and/or known alcohol and drug abuse; 3) children requiring chronic oral glucocorticoid therapy; 4) having an injury that may affect daily life activities and can be aggravated by exercise; and 5) to have a lower limb prosthesis that prevent bone assessment.

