Several studies highlight that exercise interventions delivered during cancer treatment are not successful in improving bone health nor other factors such as health-related quality of life [40, 42], suggesting a new approach focusing on post treatment phase is needed. Furthermore, following the study of McKay et al. [36], the exercise programme should be effective, possible to perform at any place, short in duration, inexpensive and simple to administer. iBoneFIT has been designed to meet all these requirements. The exercise programme will be delivered online and using social media which also guarantees social distancing nowadays. Some international physical activity interventions based on online and app-based approaches have shown promising results, indicating the suitability of this technology to influence health behaviours [103, 104]. Therefore, analysing the effect of this exercise programme in paediatric cancer survivors is of scientific interest.

iBoneFIT represents a golden opportunity to analyse for the first time the effect of a simple, feasible, inexpensive and short duration exercise programme on bone health in paediatric cancer survivors. This study will target this population in high risk of low bone mass, using an enjoyable intervention and cutting-edge technologies (i.e. DXA and tri-axial accelerometers) to assess its effectiveness. If successful, this 9-month online exercise program will likely encourage paediatric cancer survivors to be physically active or even engage in a sport, providing an opportunity to decrease chronic health conditions in the short and long terms [6]. Finally, iBoneFIT will substantially contribute to the existing knowledge of how physical activity affects quality of life and mental health in this population. The long-term medical and psychological effects of childhood cancer or its treatment may negatively affect social functioning such as school attendance, obtaining employment and even social activities [100]. Therefore, their quality of life and mental health are important concerns, and efforts have to be made to improve it, which will have an important societal and economic impact.

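### Time since last cancer treatment can range from 0 days to over 15 years at entry, is plausibly prognostic for bone change, and should be a prespecified covariate rather than left to adjustment chosen from the baseline comparison

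*Protocol article*

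**What the plan says.** The section Inclusion and exclusion criteria of the Protocol article sets four entry conditions. The child is "aged 6 to 18 years", was "diagnosed at least 1 year earlier", has "to have been exposed to radiotherapy and/or chemotherapy" and is "not currently receiving treatment for cancer". The only interval is counted from diagnosis. No interval since the last treatment appears there or elsewhere in the article. The one exclusion that touches lasting treatment effects on bone is "children requiring chronic oral glucocorticoid therapy", which covers present need and not past use.

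Under Randomization and blinding, allocation is "stratified by age and sex". Under Statistical analysis, the model has a time-by-group term with the baseline value of each outcome as covariate, and change in bone outcomes is expressed as z-scores adjusted for age and sex. The same section says that a baseline comparison of the arms will show whether more adjustment is needed. It names no variable for that adjustment.

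The Background attributes low bone density to the treatment: gonadal failure after pelvic radiation or gonadotoxic chemotherapy, pituitary dysfunction after cranial radiation, and direct radiation damage to bone. It also cites low density both during and after treatment.

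**The concern.** If the deficit comes from the treatment, how long ago the treatment ended may influence how bone changes over the next 9 months, whether or not the child exercises. The entry criteria let this interval vary very widely, and nothing fixed in advance in the design or the stated model takes account of it.

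Two things are at stake. The first is precision: variation in change that a known date could explain stays in the residual. The second is chance imbalance: with 58 children per arm, the arms can differ noticeably in the share of recent finishers. The stated safeguard, deciding on adjustment after looking at baseline differences, is weak. It ties the analysis model to the observed data, and it selects variables by how far they are imbalanced rather than by how strongly they predict the outcome.

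**Working it through.** The article states no figure on this point, so there is none to reproduce. The 58 per arm (116 in total) is taken from Sample size as given, and the point does not depend on how it was derived.

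**1. Time off therapy that the criteria permit.** Let T be months from diagnosis to the last treatment. The article gives no treatment durations, so the values of T are illustrative. Entry needs at least 12 months since diagnosis and treatment finished, so the earliest entry is max(12, T), and

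minimum time off therapy = max(12, T) − T = max(0, 12 − T).

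| T (months) | Earliest entry (months from diagnosis) | Minimum time off therapy (months) |
|---|---|---|
| 4 | 12 | 8 |
| 6 | 12 | 6 |
| 9 | 12 | 3 |
| 12 | 12 | 0 |
| 24 | 24 | 0 |
| 36 | 36 | 0 |

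The upper end is capped only by age. A child last treated at age 2 and enrolled at 18 has 18 − 2 = 16 years off therapy.

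**2. Whether the stated analysis captures it.** Age and sex strata and age- and sex-adjusted z-scores do not fix it, because children of the same age can have finished treatment at different times. The baseline value of the outcome reflects where a child stands, not necessarily how bone is changing. Two children with the same age, sex and baseline z-score may be a week or ten years off therapy. These terms may absorb part of the effect, but not by design.

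**3. Chance imbalance.** Let p be the share of recent finishers (assumed). The 95% range of the difference in shares between arms of n = 58 is ±1.96 × √(2p(1 − p)/n). At p = 0.2 this is 1.96 × √(2 × 0.2 × 0.8/58) = 0.146, about ±15 percentage points. From exact binomial distributions, the probability that the arms differ by 10 points or more is 9% at p = 0.1, 20% at p = 0.2 and 31% at p = 0.5.

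If recent finishers differ in mean change by d = 0.25 to 1 SD (assumed), an imbalance of 0.146 shifts the contrast by 0.146 × d, that is by 0.04 to 0.15 SD.

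**4. Precision.** If the covariate explains a share R² of the residual variance, omitting it leaves an effective sample of n(1 − R²), and matching the adjusted analysis needs n/(1 − R²).

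| R² (assumed) | Effective sample out of 116 | Enrolment needed to compensate |
|---|---|---|
| 0% | 116 | 116 |
| 5% | 116 × 0.95 = 110.2 | 116/0.95 = 122.1 (+5%) |
| 15% | 116 × 0.85 = 98.6 | 116/0.85 = 136.5 (+18%) |

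The loss is thus 0% to 15% of the effective sample. The 18% is the extra enrolment that offsets the 15% loss.

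As a check on the range, a two-group split raises the variance by p(1 − p)d². At p = 0.2 and d = 0.25, 0.5 and 1, the rise is 1%, 4% and 16%, which corresponds to R² = 0.01/1.01 = 1%, 0.04/1.04 = 4% and 0.16/1.16 = 14%. The extreme pair p = 0.5 and d = 1 gives a rise of 25%, or R² = 0.25/1.25 = 20%, just outside the range used.

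**The case against.** A reader might infer that counting from diagnosis contradicts the trial's rationale, or that the one-year rule is a washout that works backwards because the longest-treated children need no time off. The documents do not support this. Exercise and bone health says of an earlier programme that the necessary intensity was out of reach, since "this could not be achieved during treatment due to the child’s responses to the treatment and disease". The Discussion draws the lesson "suggesting a new approach focusing on post treatment phase is needed". The requirement that treatment is not current meets that aim, and the article nowhere calls the one-year rule a washout. Broad entry is defensible with two recruiting units. The article also handles reduced fitness and bone density by starting every participant in the exercise arm with a squat phase before jumping, so nothing in it shows that recent finishers cannot do the programme.

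A reader might also infer bias. Randomisation balances time off therapy in expectation, and chance imbalance is already allowed for in the type I error. That objection stands in full.

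Three more objections have weight. First, no section says how bone change varies with time since treatment, so the prognostic strength is unknown and could be nil. Second, baseline adjustment and z-scores may already take up part of it, and Sample size allows 10% for multivariable analyses. Third, a full covariate list usually sits in an analysis plan that is not shown, so the absence of one here is no fault. What remains is narrower: the article does state how further adjustment will be decided, namely from the observed baseline comparison, and that rule is worth replacing for a variable that the Background itself makes a plausible predictor.

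**Conclusion.** The point holds as a cheap improvement in precision, not as an error in eligibility. The criteria permit 0 days to over 15 years off therapy. How much of that range occurs depends on who is recruited. Time since treatment is plausibly prognostic on the article's own account of why these children have bone deficits, and it is neither a stratum nor a named covariate.

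The loss from omitting it is 0% to 15% of the effective sample if it explains 0% to 15% of residual variance. That range is an assumption, because the article gives no figure from which to estimate it. There is no systematic bias. Even a 15-point imbalance in recent finishers would move the contrast by only about 0.04 to 0.15 SD under the assumed differences.

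**What to change.** Record the date of last cancer treatment from the hospital record. Every participant has one, because exposure to radiotherapy or chemotherapy is an entry condition. Define once, for all children, what counts as the last treatment.

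In Statistical analysis, prespecify time since last treatment at T0, on a log scale, as a fixed covariate for the bone outcomes alongside the baseline value. Since 0 days is permitted, add a small constant such as 1 month before taking logs. State that this covariate is used whatever the baseline comparison shows, in place of choosing adjustment from observed imbalance.

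The cost is one date per child and one model degree of freedom. With all 116 analysed, and intercept, group and baseline value in the model, residual degrees of freedom fall from 113 to 112. No child is excluded and recruitment is unaffected. Whether to set a minimum interval off therapy is a clinical decision for the sponsor and is not part of this change.
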